# Study protocol: improving cognition in people with progressive multiple sclerosis: a multi-arm, randomized, blinded, sham-controlled trial of cognitive rehabilitation and aerobic exercise (COGEx)

**DOI:** 10.1186/s12883-020-01772-7

**Published:** 2020-05-22

**Keywords:** Aerobic exercise, Cognitive training, Progressive multiple sclerosis

## Abstract

**Background:**

Cognitive dysfunction affects up to 70% of people with progressive MS (PMS). It can exert a deleterious effect on activities of daily living, employment and relationships. Preliminary evidence suggests that performance can improve with cognitive rehabilitation (CR) and aerobic exercise (EX), but existing data are predominantly from people with relapsing-remitting MS without cognitive impairment. There is therefore a need to investigate whether this is also the case in people with progressive forms of the disease who have objectively identified cognitive impairment. It is hypothesized that CR and EX are effective treatments for people with PMS who have cognitive impairment, in particular processing speed (PS) deficits, and that a combination of these two treatments is more effective than each individual treatment given alone. We further hypothesize that improvements in PS will be associated with modifications of functional and/or structural plasticity within specific brain networks/regions involved in PS measured with advanced MRI techniques.

**Methods:**

This study is a multisite, randomized, double-blinded, sham controlled clinical trial of CR and aerobic exercise. Three hundred and sixty subjects from 11 sites will be randomly assigned into one of four groups: CR plus aerobic exercise; CR plus sham exercise; CR sham plus aerobic exercise and CR sham plus sham exercise. Subjects will participate in the assigned treatments for 12 weeks, twice a week.

All subjects will have a cognitive and physical assessment at baseline, 12 weeks and 24 weeks. In an embedded sub-study, approximately 30% of subjects will undergo structural and functional MRI to investigate the neural mechanisms underlying the behavioral response. The primary outcome is the Symbol Digit Modalities Test (SDMT) measuring PS. Secondary outcome measures include: indices of verbal and non-verbal memory, depression, walking speed and a dual cognitive-motor task and MRI.

**Discussion:**

The study is being undertaken in 6 countries (11 centres) in multiple languages (English, Italian, Danish, Dutch); with testing material validated and standardized in these languages. The rationale for this approach is to obtain a robustly powered sample size and to demonstrate that these two interventions can be given effectively in multiple countries and in different languages.

**Trial registration:**

The trial was registered on September 20th 2018 at www.clinicaltrials.gov having identifier NCT03679468. Registration was performed before recruitment was initiated.

## Background

A recent comprehensive review of rehabilitation studies in progressive MS (PMS) encompassing balance, weakness, cardiovascular fitness, ataxia, fatigue, bladder dysfunction, spasticity, pain, cognitive deficits, depression and pseudobulbar affect concluded that there was a striking dearth of studies devoted solely to people with secondary progressive MS (SPMS) or primary progressive MS (PPMS) [1]. Furthermore, when including progressive patients alongside patients with relapsing-remitting disease (RRMS), subject numbers has generally been very small while analysis of treatment effects have not accounted for the possible influence of disease course. Finally, in the few studies reporting benefits of treatment for patients with progressive disease, the ecological validity of the results remained uncertain.

The present study focuses on improving cognition in people with PMS for two reasons.

First, up to 70% of people with PMS are impaired in this domain [2] and second, people with MS have themselves identified cognitive dysfunction as a primary area of concern [3]. Furthermore, there are now a number of studies suggesting that cognitive rehabilitation (CR) can result in significant improvements in numerous cognitive domains. A consistent picture is emerging of CR bringing about improvements in learning/memory [4, 5] and processing speed [6, 7]. Of note is that home-based CR programs have also reported significant cognitive gains [8, 9] as have interventions administered in a group setting [10, 11]. Complementing these data are findings suggesting that exercise too can provide physical, cognitive and emotional benefits [12–14].

These results, while encouraging, are also limited by various factors including small sample size, single centre administration and sample composition predominately limited to people with RRMS. Whether people with progressive disease will derive the same benefits from these interventions is therefore not known, although a single study suggests that improvement in memory may be possible with CR [4]. The gaps in our knowledge therefore suggest a number of complementary ways forward. Multisite replication of these preliminary, promising findings is a good place to start. However, as people with progressive MS constantly remind us, time is short. This suggests that an additional effort is required, a bolder approach, one that combines more than one intervention with the aim of producing synergistic effects, an improvement in one area boosting the putative benefits of therapy in another, the overall outcome exceeding the sum of the individual treatments. Such an approach often reflects the clinical reality of PMS where multiple neurological difficulties rather than an isolated problem must be addressed simultaneously. While a powered joint CR and exercise clinical trial has yet to be done in people with MS of any disease course there is tentative evidence from three small studies in people with RRMS that this approach may be more beneficial than either intervention alone [15–17]. Thus, a methodologically rigorous, well-powered study is needed now in PMS specifically in an effort to inform clinical practice. It is only through such a study that we can ensure that final conclusions and recommendations are not limited by sample size, generalizability or methodological concerns.

## Methods/design

The protocol adheres to the Spirit guidelines.

### Aim, design and setting of the study

The study has the following primary aims:
To assess whether CR and exercise (EX) in combination have beneficial synergistic effects in the treatment of impaired processing speed in people with PMS.To determine whether CR and EX are individually effective treatments for impaired processing speed in people with PMS.

Secondary aims:
To assess the everyday life impact of cognitive and/or physical changes after the different rehabilitation interventions.To assess brain functional and structural substrates of cognitive changes after the different rehabilitation interventions.

This study is a multicenter, multi-arm, randomized, double-blinded, sham-controlled trial that includes follow up periods of 12- and 24 weeks (+/− 2 weeks) post randomization. As depicted in Fig. 1, after the baseline assessment each participant will be randomized to one of four arms with different combinations of CR and EX and their respective shams (−S). That is: CR + EX; EX + CR-S; EX-S + CR; EX-S + CR-S.

**Fig. 1 Fig1:**
[figure not shown]
Study flow-chart. RRMS, Relapsing-Remitting Multiple Sclerosis; EDSS, Expanded Disability Status Scale; CNS, Central nervous system; PMS, Progressive Multiple Sclerosis; GLTEQ, Godin Leisure-Time Exercise Questionnaire; BDI-II Beck Depression Inventory-II; SDMT, Symbol Digit Modalities Test; CR-S, cognitive rehabilitation - sham; EX-S, exercise-sham; EX, exercise; CR, cognitive rehabilitation

The study protocol will be carried out at 11 sites in six different countries (Canada (1 site), USA (2 sites), United Kingdom (2 sites), Denmark (1 site), Belgium (1 site) and Italy (4 sites)). Each site has at least one blinded and one unblinded research assistant. The blinded measurement assessor (research assistant) will screen potential participants and perform all baseline and 6-month testing, whereas the 3-month follow up interview will be made by the unblinded research assistant. If a participant meets the inclusion criteria (see later), the unblinded research assistant is responsible for randomizing participant using REDCap (a web-based system) and conducting the interventions for which the participant is assigned. As the study design aims to mask the intent of the intervention given to the participants, the unblinded research assistant will be strictly instructed not to discuss participant allocation and participants will likewise be instructed not to reveal details that can indicate their group allocation to the blinded assessor. The MRI analysis will be undertaken by experienced technicians blinded to group allocation.

### Recruitment and screening of participants

Participants are being recruited via specialized in and out-patient MS clinics, as well as via media advertising. Prior to enrollment, all potential participants will undergo a two-step screening procedure. First, a *pre-screening* examination in person or via telephone will collect basic information. If the participant passes the initial pre-screen, a detailed face-to-face screening for neurological, psychiatric, cognitive, and medical variables will take place at the participating center. Inclusion and exclusion criteria for the two screening steps are summarized in Tables 1 and 2, respectively.

**Table 1 Tab1:** Inclusion and exclusion criteria for the initial pre-screening step

	**Inclusion criteria**
Diagnosis	A definite diagnosis of PMS determined by neurologist
Age	25–65 years
Ambulation	Not wheelchair dependent (EDSS,< 7.0)
	**Exclusion criteria**
Substance abuse	Use of illicit drugs, PCP, LSD, Stimulants, Amphetamines, Barbiturates, etc. (Cannabis use is accepted).
Neurological history	Relapses in the past 3 months, a history of central nervous system disease other than PMS such as stroke, Parkinson’s disease, traumatic brain injury, etc.
Severe mental illness	Psychotic symptoms, Bipolar Disorder, Schizophrenia.
Medications	Steroid use within the past 3 months.
Transport	Unable or unwilling to travel to the center for testing and training or requiring transportation by ambulance.
Medical contradiction	No medical clearance provided by a physician upon failure of AHA/ACSM Health/Fitness Facility Pre participation Screening Questionnaire.
Current exercise activity	Currently performing enough physical activity for health benefits based a GLTEQ score > 23).

*PCP* Phencyclidine, *LSD* Lysergic acid diethylamide, *AHA* American Heart Association, *ACSM* American College of Sports Medicine, *EDSS* Expanded Disability Status Scale, *GLTEQ* Godin Leisure-Time Exercise Questionnaire, *PMS* Progressive Multiple Sclerosis

**Table 2 Tab2:** Inclusion and exclusion criteria for the second in-person interview

	**Inclusion Criteria**
SDMT	1.282 SD or more below published normative data (10th percentile).
	**Exclusion criteria**
Visual Acuity	Corrected near vision worse than 20/70 (to see the test materials). Severe nystagmus according to neurologist ratings.
The Beck Depression Inventory	Score ≥ 29 (indicative of severe depression)
Token test	Score ≥ 29 indicative of intact verbal comprehension
MRI sites only	Failing the standard MRI screening form

*MRI* Magnetic Resonance Imaging, *SDMT* Symbol Digit Modalities Test

When participants complete the study they will revert to their neurologist and usual care programs.

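### Table 2 lists the Token Test score that it labels intact as a reason for exclusion, so the criterion as printed runs against its own label

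*Protocol article*

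**What the plan says.** The section on recruitment and screening describes a telephone or in-person pre-screen followed by a detailed face-to-face screen, and points to the tables for the rules: "Inclusion and exclusion criteria for the two screening steps are summarized in Tables 1 and 2, respectively".

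Table 2 covers the second step. Its inclusion block has a single entry, the SDMT: "1.282 SD or more below published normative data (10th percentile". Its other block is headed "Exclusion criteria" and has four rows:

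- Visual acuity: "Corrected near vision worse than 20/70 (to see the test materials", with severe nystagmus added.
- Beck Depression Inventory: "Score ≥ 29 (indicative of severe depression".
- Token Test: "Score ≥ 29 indicative of intact verbal comprehension".
- MRI sites only: failure of the standard MRI screening form.

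Table 5 marks the Token Test once, at in-person screening, with no cut-off.

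**The concern.** An exclusion row should name what keeps a person out. This one names the unimpaired state. If the heading governs, as it does for every other row in the block, the trial turns away candidates with intact comprehension and keeps those who fall short of it.

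Eligibility defines the population to which the result applies. The SDMT is both the entry test and the primary outcome, and the trial reads a low score as slowed processing. A comprehension screen in the intended direction helps to protect that reading; in the reverse direction it would work against it. The instructed tasks (the scripted exercise test, the alternating-alphabet dual task, the Go/No-go familiarisation) also presuppose that participants understand what they are asked to do. Readers, replicators and later systematic reviewers will take the eligible population from this table.

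**Working it through.** No arithmetic applies. The check is a literal reading of the rule, set against its neighbours and against every other mention of the test.

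**1. Literal application.** Heading: exclusion. Condition: Token Test score of 29 or more. Label in the same row: intact verbal comprehension. It follows that:

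- score ≥ 29: labelled intact, therefore excluded;
- score < 29: not labelled intact, therefore not excluded by this row.

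Heading and label cannot both stand if the purpose is to screen out poor comprehension, and the article gives no reason for wanting to exclude people with intact comprehension.

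**2. Convention of the tables.** Table 1 has seven exclusion rows and Table 2 has four, 7 + 4 = 11 in all. Ten name the disqualifying state:

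- Table 1: illicit drug use, recent relapse or other central nervous system disease, severe mental illness, recent steroid use, inability or unwillingness to travel, no medical clearance, and a GLTEQ score above 23.
- Table 2: poor near vision or severe nystagmus, severe depression, and a failed MRI screen.

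The Token Test row is the only one of the 11 that names the unimpaired state. The tables therefore have no habit of listing the acceptable value under exclusion.

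**3. The adjacent row.** The depression row has almost the same form: a score of 29 or more, then a gloss. There the gloss is the abnormal state and meeting the condition excludes. A reader who applies the same rule to the next row excludes people with intact comprehension.

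**4. Could the text extraction have caused it?** Unlikely. The wording of the row is complete, it lies between two other exclusion rows, and the inclusion block is separate and holds only the SDMT.

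**5. Is it corrected elsewhere?** No. Table 5 gives timing only. The section on neuropsychological evaluation does not mention the Token Test. The flow chart (Fig. 1) is not available to this review, and neither is the full protocol.

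**6. Reach.** The power analysis uses assumed SDMT changes, their standard deviation and the group size. None of these refers to the Token Test, so no sample size or power figure changes.

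**The case against.** The strongest reply is that the row explains itself. Unlike the depression row, its gloss is not in parentheses, so it can be read as a note that 29 or more counts as intact, with failure to reach 29 as the implied exclusion. Most clinicians would guess that intention. The article also says that the tables summarise the criteria, that assessments are manualised, that assessors were trained before recruitment, and that data forms carry validation and skip logic. Sites worked from those documents, not from an article published after recruitment had begun.

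Much of this stands. It makes a drafting error the likely explanation and a reversed rule in practice improbable. It does not make the printed criterion right. A reader has to override the heading to reach the sensible meaning, and nothing in the article confirms that meaning.

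A reader might also infer three stronger things that the article does not support:

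- **That the rule would select people who cannot follow instructions.** The article labels only scores of 29 or more. It gives no range or grading for lower scores, so below 29 means no more than below the cut-off labelled intact.
- **That the value 29 was carried over from the depression row.** Two scales can share a cut-off by coincidence. If text was carried over, the number itself would be in doubt and not only the direction, which is why the threshold also needs confirming.
- **That participants already enrolled were wrongly screened.** Nothing in the article shows this.

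**Conclusion.** The point holds as an internal contradiction in one eligibility row. As printed, the criterion excludes everyone whose score it calls intact and admits only those below that cut-off, and no other part of the article corrects it. An eligibility rule that the article chooses to print is not detail left to a fuller document, so it needs correcting.

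The consequence for the trial itself is conditional. By March 2020, 135 of the planned 360 participants had been randomised (135/360 = 37.5%). That figure shows how many records would be in question if the reversed rule had been used; it is not an estimate of how many were affected. The conclusion rests on the heading and label as printed and on the other rows following the usual convention. It assumes nothing about what scores below 29 mean clinically, and it does not depend on how the error arose.

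**What to change.** 1. Compare the Token Test row with the full protocol and the REDCap screening form on three points: heading, direction and threshold.
2. Correct the row so that it agrees with its own label. If 29 is confirmed as the cut-off, either list a score of 29 or more as an inclusion criterion or state the exclusion as a score below 29. If the full protocol gives another value, the row should follow that document.
3. Check that the site manuals agree with the form.
4. Review the Token Test records of participants already randomised only if the form or the manuals are found to carry the reversed rule. If they do not, a one-line correction to the article is enough.

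Steps 1 to 3 cost one table row and a short check of the form and manuals. Step 4 would be a query on existing screening records. No analysis or sample size work is needed.

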### Randomization

Participants will be randomized to a treatment arm using block randomization by site. Block sizes will be blinded to study personnel and principal investigators. Randomization assignment will be conducted in REDCap (a secure web application for building and managing databases) within 24 h after the baseline assessment.

### Interventions

For all interventions, comprehensive manuals were developed and distributed to all participating sites to ensure optimal standardization. This was complemented by face-to-face and distance training at the beginning of the study, and supplemented as necessary during the course of the study. All interventions will be delivered within the hospital/clinic setting or research center under individual supervision, twice per week over a 12 week period. All intervention sessions will start with either CR or CR-S followed by EX or EX-S. In case of holiday, sickness or other unforeseen circumstances the intervention period may be extended by up to two additional weeks, allowing the intervention period to be a maximum of 14 weeks. During the intervention period, compliance to the exercise prescription (attended/planned sessions; actual intensity/target intensity; actual duration/target duration) and cognitive rehabilitation protocols will be monitored by an independent person who will provide regular feedback to sites to optimize the fidelity of the treatment regimens.

Any potential reason for discontinuing will be discussed on individual basis between the principal investigator of the site and the Data Safety Monitoring Board. If a situation occurs where precaution has to be taken in order for the participant to continue in the study, unblinding will be permissible if permitted by the study steering committee.

#### Cognitive rehabilitation (CR)

The CR component comprises the computerized RehaCom program (Pearson’s Clinical Assessment group, Bloomington, MA, USA) that will be performed on non-consecutive days. To address processing speed, the modules “divided attention 1 and 2”, “attention and control”, “sustained attention” and “vigilance 2” will be used. Participants will begin at level 1 and advance the program as dictated by their performance. Each session will be programmed to last 45 min. The RehaCom program has previously been shown to have positive effects on processing speed in persons with RRMS [6, 8, 18].

#### Sham cognitive rehabilitation (CR-S)

The CR-S consists of Internet training [19], beginning with more basic tasks such as learning to use a computer and the internet to search for information, including locating information regarding medications, gardening, getting directions, etc. Each session is programmed to last 45 min and will also take place on non-consecutive days. The control session is designed to match the CR on social and computer contact. Similar training procedures have previously been shown not to impact PS in a normal aging sample [19].

#### Exercise (EX)

The exercise intervention is aerobic and performed on a recumbent stepper (NuStep T5XR, Ann Arbor, MI, USA). All sessions are supervised and performed on an individual basis. Training is performed on non-consecutive days thereby permitting recovery between sessions. The EX intervention consists of twice weekly sessions, one of which is continuous exercise and the other of which is high intensity interval training. It complies with the basic principle of progressive overload. The continuous training ranges from 10 min of exercise at a work rate corresponding with 50–60% of VO_2_peak at week one, progressing to 30 min of exercise at a work rate corresponding with 70–80% of VO_2_peak in week 12. The interval training begins with 5 × 1 min of exercise at a work rate corresponding with 80–90% VO_2_peak followed by 1 min of active breaks with a work rate at 15 watts. At week 12 the protocol will have progressed to 10 × 2 min of exercise at a work rate corresponding with 90% VO_2_peak followed by 2 min of active breaks with a work rate of 15 watts. Protocols built on the same principles have previously improved VO_2_peak in persons with MS [20, 21]. The recumbent stepper represents an acceptable modality of aerobic exercise in people with PMS [22] as has interval training using this device. See Table 3 for further details.

**Table 3 Tab3:** The progressive aerobic exercise protocol

**Week**	**Session 1 (Continuous training; CT)**	**Session 2 (High Intensity Interval Training; HIIT)**
1	CT (10 min @ WR ~ 50–60% VO2peak)	HIIT (5, 1:1 work:rest intervals; work for 1 min @ WR ~ 80–90% VO2peak, rest for 1 min at 15 W)
2	CT (15 min @ WR ~ 50–60% VO2peak)	HIIT (5, 1:1 work:rest intervals; work for 1.5 min @ WR ~ 80–90% VO2peak, rest for 1.5 min at 15 W)
3	CT (20 min @ WR ~ 50–60% VO2peak)	HIIT (5, 1:1 work:rest intervals; work for 2 min @ WR ~ 80–90% VO2peak, rest for 2 min at 15 W)
4	CT (25 min @ WR ~ 50–60% VO2peak)	HIIT (6, 2:2 work:rest intervals; work for 2 min @ WR ~ 80–90% VO2peak, rest for 2 min at 15 W)
5	CT (30 min @ WR ~ 50–60% VO2peak)	HIIT (7, 2:2 work:rest intervals; work for 2 min @ WR ~ 80–90% VO2peak, rest for 2 min at 15 W)
6	CT (30 min @ WR ~ 50–60% VO2peak)	HIIT (8, 2:2 work:rest intervals; work for 2 min @ WR ~ 80–90% VO2peak, rest for 2 min at 15 W)
7	CT (30 min @ WR ~ 60–70% VO2peak)	HIIT (9, 2:2 work:rest intervals; work for 2 min @ WR ~ 80–90% VO2peak, rest for 2 min at 15 W)
8	CT (30 min @ WR ~ 60–70% VO2peak)	HIIT (10, 2:2 work:rest intervals; work for 2 min @ WR ~ 80–90% VO2peak, rest for 2 min at 15 W)
9	CT (30 min @ WR ~ 65–75% VO2peak)	HIIT (10, 2:2 work:rest intervals; work for 2 min @ WR ~ 90% VO2peak, rest for 2 min at 15 W)
10	CT (30 min @ WR ~ 65–75% VO2peak)	HIIT (10, 2:2 work:rest intervals; work for 2 min @ WR ~ 90% VO2peak, rest for 2 min at 15 W)
11	CT (30 min @ WR ~ 70–80% VO2peak)	HIIT (10, 2:2 work:rest intervals; work for 2 min @ WR ~ 90% VO2peak, rest for 2 min at 15 W)
12	CT (30 min @ WR ~ 70–80% VO2peak)	HIIT (10, 2:2 work:rest intervals; work for 2 min @ WR ~ 90% VO2peak, rest for 2 min at 15 W)

*WR* Work rate, *CT* Continuous training, *HIIT* High intensity interval training

